Previous studies have demonstrated that digitally presented yawning videos can elicit contagious yawning responses in humans [22,23], and even across species, such as in chimpanzees and orangutans exposed to digital or android yawning stimuli [24,25]. However, it remains unclear whether digitally presented yawning stimuli, particularly those generated by animal characters, are associated with sleepiness-related responses when assessed using multimodal psychophysiological measures.

Understanding whether exposure to yawning stimuli is associated with changes in sleepiness has important implications for both sleep research and the design of technologies intended to modulate arousal or relaxation [2]. Accordingly, this study seeks to advance this line of research by examining yawning videos featuring either humans or digital characters, presented with and without auditory cues, and assessing their associations with subjective and physiological indicators of sleepiness under controlled conditions. The protocol was developed to investigate four research questions: (1) whether exposure to human yawning videos is associated with sleepiness-related responses, (2) whether digital character yawning elicits comparable effects, (3) whether auditory yawning cues modulate these responses, and (4) how individual differences influence these associations.

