### Phase 2: experimental sessions

The experimental phase consists of two intervention sessions conducted on separate days with a minimum one-day interval to minimize potential carryover effects related to fatigue or transient sleepiness. Each session corresponds to one stimulus type (human yawning vs. digital character yawning), with session order randomized across participants. Each session will follow an identical structure and last approximately 70 min. To minimize circadian confounding, experimental sessions will be scheduled at approximately the same time of day, typically between 14:00 and 16:00, consistent with prior findings that yawning exhibits circadian variation in both animals and humans [30,31]. The second session will be conducted within ±1–2 h of the first session whenever feasible. Sessions will be scheduled to avoid early morning or late evening when spontaneous yawning frequency is known to be naturally elevated [14,32,33].

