Exploratory outcomes will include behavioral indicators of sleepiness, such as yawning occurrence and instances of sleep onset observed during the experiment. Additional exploratory analyses will examine the relationship between yawning behavior and both subjective and physiological outcomes. These relationships will be modeled using mixed-effect approaches where appropriate, which allows for the inclusion of both within-subjects (e.g., condition, time) and between-subjects (e.g., chronotype, baseline sleep quality) factors.

Statistical significance will be evaluated using two-sided tests with an alpha level of 0.05 unless otherwise specified. Results will be reported using effect sizes (e.g., estimated mean differences as quantified by Cohen’s *d* or Hedge’s *g*) alongside 95% confidence intervals and p-values. Given the exploratory nature of several outcomes, findings will be interpreted with appropriate caution, and emphasis will be placed on the direction, magnitude, and consistency of observed effects rather than statistical significance alone. The data analysis plan is summarized in Table 2.

**Table 2 tbl0002:** Data analysis plan.

Analysis Level	Procedure
Primary outcome analysis	▪ Analyze changes in KSS using linear mixed-effects models to account for the within-subject repeated-measures design ▪ Fixed effects will include stimulus type (human vs digital character yawning), auditory condition (with sound vs without sound), and their interaction. ▪ Subject will be included as a random effect with a random intercept to account for interindividual differences in baseline sleepiness. ▪ Where model convergence permits, random slopes for condition effects may be explored. ▪ Conduct planned comparison [50] to examine differences in subjective sleepiness between human and digital yawning stimuli, differences between auditory conditions (with vs without sound), and the interaction between stimulus type and auditory condition.
Secondary outcome analysis	▪ Apply the mixed-effects modeling framework used for primary outcome analysis to each physiological outcome, including HRV, EDA, skin temperature, pupil dynamics, and fNIRS measures. ▪ Analyses will focus on changes relative to baseline and associations with experimental conditions. ▪ Where appropriate, multiple comparison adjustments (e.g., Bonferroni or false discovery rate correction) will be reported as supplementary information.

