Exploratory analysis	▪ Examine sleep onset occurrence and sleep onset latency based on behavioral and physiological indicators. ▪ Count observable yawning events by condition. ▪ Examine the relationship between yawning frequency and outcome measures (KSS scores and physiological measures) using mixed-effect models. ▪ Where temporal resolution permits, conduct event-based analyses to examine short-term physiological responses surrounding yawning events. ▪ Explore moderation effects by including interaction terms in mixed-effects models (e.g., chronotype, habitual sleep quality, baseline sleepiness, and personality traits).
Model diagnostics	▪ Inspect Q-Q plots of residuals to assess normality. ▪ Plot residuals vs fitted values to check homoscedasticity. ▪ Use formal diagnostic tests where appropriate (Shapiro-Wilk, Breusch-Pagan). ▪ Report any violations and their potential impact on inference and apply transformations if necessary.

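### With only a subject intercept fixed in Table 2, the trait-by-condition tests and the planned sound and type contrasts have an error rate that depends on unstated variances and can fall above or below 5%

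*Protocol article*

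**What the plan says.** All of this is in the protocol article.

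- **Fixed effects** (Data analysis, Table 2, primary outcome row): "Fixed effects will include stimulus type (human vs digital character yawning), auditory condition (with sound vs without sound), and their interaction". The same row plans comparisons of human with digital, of sound with silence, and of their interaction.
- **Random effects** (same row): "Subject will be included as a random effect with a random intercept to account for interindividual differences in baseline sleepiness". It then adds: "Where model convergence permits, random slopes for condition effects may be explored".
- **Secondary outcomes** (Table 2): the primary modelling framework is reused for each physiological outcome.
- **Moderation** (Table 2, exploratory row): "Explore moderation effects by including interaction terms in mixed-effects models (e.g., chronotype, habitual sleep quality, baseline sleepiness, and personality traits". The row names mixed models but no random structure. It is the row that serves the fourth research question in the Background, "how individual differences influence these associations".
- **Design** (Phase 2): "Each session corresponds to one stimulus type (human yawning vs. digital character yawning), with session order randomized across participants". Sound therefore varies within a session, and stimulus type varies between days.
- **Error level** (Data analysis): "Statistical significance will be evaluated using two-sided tests with an alpha level of 0.05 unless otherwise specified". The text adds that findings on exploratory outcomes will be read with caution.

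**The concern.** A subject intercept absorbs differences between people in their overall level of sleepiness. It does not absorb differences in how people respond to sound or to stimulus type. A trait-by-sound test asks whether a person's sound effect depends on the trait, so its proper error is the spread of that effect between people. Likewise, the error for trait-by-type is the person-to-person spread of the human-minus-digital difference, which also carries day-to-day variation because the two types are seen on different days.

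The intercept-only model uses a single pooled residual for all of these. If one contrast varies more than the others, its test is too liberal and the tests of the others too conservative. Research question 4 presupposes that people respond differently, which is the situation in which the pooled error fails.

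Two things are at stake. One is moderators reported where none exist, or missed where they do. The other is confidence intervals of the wrong width, for moderation and also for the planned sound and type contrasts of the primary outcome.

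**Working it through.** **Inputs from the documents.** Two-sided alpha of 0.05; four post-condition ratings per person in a 2 × 2 layout; random intercept for subject; stimulus type tied to session. The documents give no sample size, SD or variance component, so everything below that depends on them is an assumption shown over a range.

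**Set-up.** Four ratings give each person three within-person contrasts: sound, type, and their interaction. Put all three on the scale where pure residual error gives variance s². Define:

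- x = variance of the personal sound effect ÷ s²;
- u = excess variance of the type contrast ÷ s². It comes from personal differences in the type effect, from day-to-day variation, or from both. Day variance contributes 2 × (day variance ÷ s²), because the contrast is a difference between two days.

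With complete, balanced data and no personal variation in the interaction, the contrast variances are s²(1 + x), s²(1 + u) and s². The intercept-only model averages them to s²[1 + (x + u)/3].

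**Formulas.** Ratio of true to assumed error variance:

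- trait-by-sound: VR = (1 + x) / (1 + (x + u)/3)
- trait-by-type: VR = (1 + u) / (1 + (x + u)/3)

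Large-sample size = 2 × [1 − Φ(1.96/√VR)]. The planned sound and type contrasts have the same ratios.

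**Reproducing the plan's figure.** At x = u = 0, VR = 1 and the size is 5.0%, the stated level.

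**Trait-by-sound.**

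| x | no type or day variance (u = 0) | equal type heterogeneity (u = x) | equal type heterogeneity, day SD = residual SD (u = x + 2) |
|---|---|---|---|
| 0.25 | 6.8% | 5.8% | 1.8% |
| 0.5 | 8.4% | 6.5% | 2.4% |
| 1 | 11.0% | 7.4% | 3.4% |
| 2 | 14.4% | 8.4% | 5.0% |

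Example, x = 1 and u = 0: VR = 2/1.333 = 1.5, and 1.96/√1.5 = 1.60, giving 11.0%. The assumed standard error is then too small by √1.5 = 1.22; at x = 2 the factor is √1.8 = 1.34. With no personal sound effect at all and u = 2, VR = 1/1.667 = 0.6 and the size is 1.1%.

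**Trait-by-type, no sound heterogeneity (x = 0).**

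| u | VR | size |
|---|---|---|
| 1 | 2/1.333 = 1.50 | 11.0% |
| 2 | 3/1.667 = 1.80 | 14.4% |
| 4 | 5/2.333 = 2.14 | 18.1% |

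Sound heterogeneity lowers these. At u = 2, x = 1 gives 11.0% and x = 2 gives 8.4%.

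**Simulation of the balanced-data test** (6,000 runs per setting; N = 20, 40 and 80 assumed). At N = 40, trait-by-sound was 10.1% for x = 1, u = 0 and 14.6% for x = 2, u = 0. For x = 1, u = 2 it was 5.3%, with trait-by-type at 11.3%. Results at N = 20 and 80 were similar.

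**After the fix.** Testing trait-by-sound against the person's own sound contrast gave 4.5% to 5.4% in every setting and at every N tried. A coarse check with fitted mixed models (N = 40, 120 data sets per setting) gave about 4% to 7% with slopes for sound and type.

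**The case against.** Four points can fairly be made for the plan.

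1. *The moderation row does not prescribe an intercept-only model.* This is true. The secondary row reuses the primary framework explicitly, and the exploratory row does not. The reading rests on the stated default and on the absence of any other error term. The planned sound and type contrasts, however, sit in the very row that fixes the intercept, so for them the point does not depend on that inference.
2. *Optional slopes already cure the problem.* A reader might infer that they cannot, because an intercept plus slopes for type, sound and interaction puts four random coefficients on four ratings. The plan does not require the interaction slope. Slopes for sound and type alone are identifiable, are already permitted, and restore roughly the nominal size. What remains is that they are optional and decided by convergence. Convergence does not show which error term a test needs.
3. *The inflation may be small or absent.* A reader might take the figures to mean that false moderators by sound occur at up to about three times 5%. The documents do not support this. Such a rate needs a sound-slope variance of about 2.2 times the residual with type and day variance at zero. It is no ceiling there either, since the limit is 25.8%. If type heterogeneity at least equals sound heterogeneity, the size cannot exceed 11.0%, and with enough day variance the sound test is conservative.
4. *The analysis is exploratory and will be read with caution.* This lowers the weight for research question 4. It does not cover the planned contrasts on the primary outcome. The shift of emphasis to effect sizes with 95% intervals does not help either, because those intervals use the same error term.

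**Conclusion.** The point holds in a limited form. Followed as written, Table 2 gives the trait-by-condition tests and the planned sound and type contrasts an error term that is right only if the sound and type contrasts carry no more variance than the residual, or if the excesses happen to balance. The direction of the error cannot be settled from the documents. Within the assumed ranges, trait-by-sound runs from about 1% to 14%, and trait-by-type is about 11% to 18% when it alone carries excess variance. Since stimulus type is tied to day, trait-by-type is the more exposed test under day-to-day variation.

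These figures assume complete, balanced data, a large-sample approximation supported by simulation, and no personal variation in the interaction. A trait's main effect on overall sleepiness is not affected in this way. Given the exploratory label on moderation, this is a modest correction, with somewhat more weight for the planned contrasts.

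**What to change.** In Table 2:

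- Test each trait-by-condition term by regressing the person's own contrast on the trait: mean of the sound films minus mean of the silent films, and mean of the human films minus mean of the digital films. Equivalently for complete, balanced data, always include subject-by-sound and subject-by-type variance components, without the interaction slope.
- Use the same error terms for the planned sound and type contrasts, and carry them over to the secondary outcomes that reuse the framework.
- Delete the clause that makes slopes conditional on convergence.

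The cost is wording only; no new data are needed. Error degrees of freedom fall. For a trait-by-condition term with a full set of trait interactions, they go from 3(N − 2) to N − 2, which at an assumed N of 40 is 114 to 38. Intervals will usually be wider, although an interval that the pooled residual had made too wide will narrow. A person who misses a session has no human-minus-digital contrast, so the variance-component version is preferable if data are incomplete.

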### Limitations

Several limitations should be acknowledged. First, the laboratory-based setting may limit ecological validity relative to real-world contexts in which yawning and sleepiness naturally occur. Second, the protocol does not include a non-yawning control condition. Although baseline and post-condition measurements allow for within-subject assessment of state changes, the absence of a neutral comparison condition limits the ability to attribute observed changes uniquely to yawning stimuli, as alternative explanations such as time-on-task effects, fatigue, or repeated exposure cannot be fully excluded. Third, while behavioral indicators of sleep onset and physiological correlates of reduced arousal will be assessed, the study does not include polysomnography. Therefore, precise sleep onset latency cannot be determined. Despite these limitations, this protocol establishes a methodological framework for investigating how human-like behavior presented by digital agents is associated with subjective and physiological states, which provides a foundation for future confirmatory studies and real-world deployments.

Findings from executing this protocol will have several important implications. From a theoretical perspective, it contributes to a more functional understanding of whether exposure to contagious yawning stimuli is associated with changes in sleepiness and arousal regulation, rather than focusing solely on yawning frequency. By integrating subjective, physiological, and behavioral indicators, the study informs ongoing debates regarding the potential role of yawning stimuli exposure in sleep-related state modulation. From an applied perspective, the findings may inform the design of non-pharmacological approaches for modulating arousal and relaxation. In particular, evidence that digitally presented yawning stimuli are associated with sleepiness-related responses would have implications for the design of AI-driven avatars, digital companions, and interactive health technologies, where subtle behavioral cues may be leveraged to influence user state without explicit instruction.

Importantly, even in the absence of strong effects, the study will help delineate the conditions under which exposure to contagious yawning stimuli is not meaningfully associated with sleepiness-related states. Such null or weak findings would provide valuable insight for refining theoretical models and informing the design of future digital interventions.

## Related research article

None*.*

## Data Availability

No data was used for the research described in the article.
